### Step 3: Selection of Theory-Based Methods and Practical Applications

In Tables 2 and 3, an overview of the methods and practical applications used in the intervention is given for the motivational and volitional phases, respectively. For example, the selected theoretical method *stating implementation intentions* corresponded with the determinants *action planning*, and *coping planning*.

To translate the methods into practical applications, we used study protocols of effective interventions [25-28,41-45]. We also used methods incorporated in an original program from our research group developed by Vandelanotte et al [27] and Spittaels et al [28]. This original program gave only feedback on motivational determinants (eg, intentions, attitudes, and knowledge). To effectively translate techniques that also target volitional determinants into practical applications, we used the programs of van Genugten et al [41], Walthouwer et al [25], and Springvloet et al [26]. For example, a practical application that was formulated by the method of *implementation intentions* to target *coping planning* was to let adults formulate a coping plan by formulating if/then plans (ie, implementation intentions). After the “if” is determined, selected difficult situations or barriers are stated. After the “then” is determined, selected solutions to overcome these difficult situations and barriers are stated (eg, *If* it is Monday evening and I am not in the mood for sports, *then* I call my friend to go to the aerobic lessons together).

**Table 2 table2:** Methods and practical applications used in the intervention for the motivational phase.

Methods	Determinants	Practical applications
General information	Risk awareness	General information is provided in the form of short texts and slogans. In these texts and slogans, physical activity guidelines and health benefits of sufficient physical activity levels are highlighted.
	Outcome expectancies	Adults can read information about physical activity and select the information that they are interested in on a website. They can, for example, select to read information about positive outcomes due to sufficient physical activity levels or information about the benefits of increasing physical activity levels.
Monitoring, tailored feedback, and personal risk information	Risk awareness	After filling in a questionnaire about physical activity level, personal feedback is provided in which adults’ levels of physical activity are provided, as well as how these compare to the recommended level.
Tailored feedback and modelling	Preaction self-efficacy	The tailored feedback includes stories about peers who succeeded in increasing physical activity levels, also in difficult situations. For example, “Eric (40 years old) decided to be more physically active in his free time, by walking in the local park for 30 minutes, three times per week. When it was raining, Eric decided to go swimming instead of walking.”
Prompting identification of barriers and problem solving, and tailored feedback	Preaction self-efficacy	A predefined list of possible difficulties (barriers and risk situations) to increase physical activity level is provided and adults can select these difficulties that are applicable to them. Based on their answers, tailored information and tips for solutions to overcome the indicated barriers and risk situations are provided; adults can select those solutions to apply which they are confident about.

**Table 3 table3:** Methods and practical applications used in the intervention for the volitional phase.

Methods	Determinants	Practical applications
Selecting hindering factors/barriers and solutions Implementation intentions	Action planning Coping planning	Adults can first select hindering factors and barriers out of a predefined list. When applicable hindering factors and barriers are not available in the list, participants also have the possibility to write down another factor or barrier in an open-ended format. Next, participants can select solutions out of a predefined list or write down another solution. Afterward, participants are stimulated to make action plans and coping plans by formulating if-then plans (ie, “implementation intentions”). After the “if,” a situation or the previously selected difficult situations or barriers are stated and after the “then” the selected action or solutions to overcome the difficult situations and barriers are stated (eg, If it is Monday evening and I am not in the mood for sports, then I call my friend to go to the aerobic lessons together). Adults can formulate this implementation intention plan in an open-ended question format on the website.
Goal setting	Action planning	A list with personal and relevant goals is formed based on previous answers; adults can select the goals to change that they are confident about.
Stating SMART^a^goals	Action planning	Adults are guided by questions to make a *specific*, *measurable*, *attainable*, *relevant*, and *time-bound* (SMART) action plan. For example, adults can formulate answers to questions on what they want to do (eg, increase physical activity by biking 20 minutes to work), how often (eg, three times per week), when (eg, Monday, Wednesday, and Friday), and when they want to start (eg, starting on Monday, July 7). After answering all the questions, the personal action plan and the if/then plan are automatically generated and sent by email to the participant.
Public commitment	Social support	Adults can choose to send their action plan to others (eg, family and friends) to ask them to support them and invite them to also make an action plan.
Prompt self-monitoring of behavior and prompt review of behavioral goals	Action planning Maintenance self-efficacy	Adults are asked to keep a record of their physical activity levels or fruit and vegetable intakes by one of the given suggestions (ie, personal paper agenda, mobile phone, Excel sheet, or online agenda). After the active goal pursuit was started, adults are also invited by email to report their behavior on the website. Periodic email reminders are sent to invite adults to fill out a questionnaire about the target behavior and their goals on the website. The results are compared with their previous behavior and goals, and iterative feedback is provided on the progress of behavior change.
Set tasks on a gradient of difficulty	Maintenance self-efficacy	When adults have attained their goals, they are invited to change the goal by reformulating a more attainable or more difficult goal or by setting additional goals.
Planning coping responses	Coping planning Maintenance self-efficacy	Adults are asked whether they experienced barriers while pursuing their goals. If so, they are invited to identify solutions to cope with the identified situations or barriers. Adults can again select solutions from a list that is generated based on the selected difficulties.
Prompt review of behavioral goals and personal feedback	Recovery self-efficacy	When people do not achieve their goals, people get personal feedback that informs them that relapse is normal. They are also advised to try again, to choose other strategies, or to adapt their goals to more attainable goals.

^a^SMART: specific, measurable, attainable, relevant, and time-bound.

### Step 4: Producing the Program and Materials

MyPlan 1.0 was programmed in the freely available software LimeSurvey 2.0 [46]. In what follows, the intervention program is discussed; an overview of the intervention program is given in Figure 1. MyPlan 1.0 consisted of three modules—fruit, vegetables, and PA—that are available on a website and on a tablet computer. Participants can log in, choose a behavior of interest, and run through the first session of the chosen health behaviors.

In the first session, people fill out a questionnaire and receive tailored feedback about how their behavior compares to the health norms. Next, adults can select and read more information about the behavior (eg, in relation to diseases and health) and can make an action plan. To make an action plan, adults first have to indicate whether they expect difficulties in changing their health behaviors. If so, adults can select or formulate barriers and reflect upon possible solutions to overcome the barriers. Afterwards, adults can make an if/then plan and an action plan by reading tips and filling in questions about how, when, and where they will act on their behavior. Based on the answers, an action plan is generated by the computer’s algorithm (see Figure 2).

It is proposed that participants monitor their behavior when they start pursuing their goals, and are invited to send their action plan to friends or family. When session 1 is completed, the action plan is emailed to the participant. A week after adults make their action plan, they receive an email with a link to the website where they can evaluate whether their formulated goal was accomplished. The current behavior is compared with the previous behavior and health goals, and iterative tailored feedback is provided. Based on this feedback, participants can decide to further pursue their goal, or to adapt their goal to a more difficult or more attainable goal. Participants also have the opportunity to reflect on encountered difficulties and to search again for solutions. The last session has a similar structure as session 2, and is available 1 month after completing session 1. At the end of session 3, patients are also referred to the module *Own Choice* on the website. This is an extra module, which participants can use at any time to adapt or to create an action plan for a behavior of their choice (eg, water intake). In this module, the same framework (ie, what, when, where, how many times, with who, and if/then) is used to enable adults to make a new action plan.

A further task in Step 4 is to test the feasibility, acceptability, and user-friendliness of the intervention [23,47]. Therefore, a specific study was conducted to address these issues, and its results are reported in a separate publication [48]. Briefly, 194 adults who used the MyPlan 1.0 intervention filled out an online questionnaire containing items about quality, user-friendliness, and applicability of the content and information architecture (ie, organization and delivery of the content) of the intervention. The results indicate that the program was generally well accepted, including for participants with a low educational level and for older participants. Nevertheless, to make the program more comprehensible for the different groups, the questions, answer options, and advice were made shorter and clearer [48]. To test the acceptability and user-friendliness of the tablet as a delivery mode, we conducted a thinking-aloud test with 40 adults. Most participants indicated that it was easy to use the intervention program on a tablet. Examples of comments that were reported were as follows: “text is too small to read on a tablet,” “moving from one page to another is too slow,” “and a pen to tick the answers would be useful.” Based on the comments, the intervention program was further adapted for appropriate use on the tablet.

**Figure 1 figure1:**
[figure not shown]
Overview of the intervention program.

**Figure 2 figure2:**
[figure not shown]
My Action plan: Example of an action plan for physical activity.

### Step 5: Development of a Program Adoption and Implementation Plan

GPs who participated in the focus group interviews were positive about the use of a computer-tailored program that provides personal advice. GPs also appreciated that they did not need the expertise and time to compose personal advice for every patient, and may restrict their role to simply motivating and advising patients to use the intervention. However, doubts were raised on how to implement MyPlan 1.0 in general practice. By using tablets, MyPlan 1.0 patients can directly experience the use of the program and discuss their advice with their GP [49]. However, GPs indicated that in some situations it is not possible to use a tablet. For example, when there is not enough time, or when patients cannot work with a tablet. Therefore, it was decided to use a combination of flyers and tablets. Patients receive a flyer with a personal code in general practice, and can decide whether they start the program in general practice on a tablet or back at home at the website. On the flyer, it is also mentioned that participants can choose whether they want to discuss their personal advice and action plan with their GP in a following consultation. To briefly discuss the personal advice and action plans of patients, every participating GP received an information letter and attended a personal information session. In this session, GPs were instructed to emphasize the importance of personal and attainable health goals, rather than prescribing health recommendations and general information. GPs' opinions also differed about when to offer the intervention in general practice, indicating that different ways to use the program in general practice and solutions with different choices on how and when to use the program must be offered to GPs. Based on these results, it was decided to provide several modes of delivery that may be applicable in different workflow systems in general practice. Therefore, a decision tree (see Figure 3) with different choices on how to deliver the intervention in general practice was developed. In this way, GPs can autonomously decide which method is suitable for their own working system, for different patients, and for different circumstances. Other results of the focus group interviews are reported in more detail elsewhere [50].

**Figure 3 figure3:**
[figure not shown]
Decision tree for GPs: General practitioners can use the decision tree to decide on how to implement the intervention in general practice.

### Step 6: Evaluation of the Program

A clustered quasi-experimental trial with three conditions will be used to evaluate the intervention (see Figure 4). We use a quasi-experimental design in which participants can be part of three different groups. First, a researcher recruits patients and randomly allocates them into an intervention (Group 1) or control group (Group 2). Next, a GP recruits patients into the other intervention group (Group 3). In both intervention groups, participants will not be randomly allocated to one of the behavior groups of the intervention (ie, PA, fruit, or vegetables), but participants can choose themselves for which behavior they want to complete the intervention. Group 1 is an intervention group in which researchers select and motivate adults to use the intervention by offering a flyer and/or tablet. In Group 3, the selection and motivation of adults will be randomly conducted by GPs in the waiting room by offering a flyer and/or tablet. Participants of both groups will receive a flyer with a personal code and can choose to start the intervention program in general practice on a tablet or at home on the website. Group 2 will be a waiting-list control group in which adults are randomly selected by a researcher. Participants in this control group only have to fill in a questionnaire and have no access to the computer-tailored feedback, action planning part, or to the evaluation in the follow-up modules. After completing the questionnaire at baseline and at the 1-month follow-up, the control group will also get access to the intervention modules.

In total, 30 adults will be selected in each of 15 general practices (n=450). First, a researcher will select 10 patients that will be allocated to the intervention group and 10 patients that will be allocated to the control group. Next, GPs will be asked to recruit another 10 patients to complete the intervention program. In this way, it can be evaluated whether GPs' involvement leads to more sustained use of the eHealth intervention, and higher levels of PA and FV intake. In both intervention groups, adults will be invited to complete session 1 either on a tablet in general practice or on their computer at home. Adults who do not use the tablet have to fill out a short questionnaire and leave their email address to be sent a reminder email to complete session 1 at home. After 1 week and 1 month of completing session 1, adults will receive an email to respectively start sessions 2 and 3. In the control group, adults will have to fill out a questionnaire at baseline in general practice or at home and at 1-month postintervention. To prompt adults to complete all questionnaires and sessions, reminder mails and SMS text messages will be sent. Inclusion criteria for participating in the study in both intervention and control groups are as follows: at least 18 years old, understand Dutch language, have an email address, and have access to the Internet. The outcome measures—increase in PA level, increase in FV intake, and self-regulation skills from baseline to postintervention—will be compared for the control and intervention conditions by conducting repeated measures multivariate analyses of variance (MANOVAs). Participant characteristics (ie, socioeconomic status [SES], age, sex, health status, and reaching health norms) will be compared at baseline. Characteristics that differ for the intervention and control groups will be added as covariates in further analyses. Furthermore, multilevel analyses will be conducted to take into account the clustering of participants into general practices.

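### Step 6 gives conflicting accounts of how Groups 1 and 2 are formed, and a full Group 1 baseline appears to depend on starting the program

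*Protocol article*

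**What the plan says.** All references are to the protocol article.

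**Formation of the groups (Step 6: Evaluation of the Program).** The sequence is given first as recruitment followed by randomisation: "a researcher recruits patients and randomly allocates them into an intervention (Group 1) or control group (Group 2"). A few sentences later the two arms are described separately. For the intervention arm: "Group 1 is an intervention group in which researchers select and motivate adults to use the intervention by offering a flyer and/or tablet". For the control arm: "Group 2 will be a waiting-list control group in which adults are randomly selected by a researcher". What the control arm is asked to do follows: "Participants in this control group only have to fill in a questionnaire and have no access to the computer-tailored feedback". Its members get the modules after the 1-month follow-up. Later in Step 6 the numbers per practice are given: "a researcher will select 10 patients that will be allocated to the intervention group and 10 patients that will be allocated to the control group".

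**Place of the baseline measurement.** Step 4 (Producing the Program and Materials) puts the intervention arm's behavior questionnaire inside the program: "In the first session, people fill out a questionnaire and receive tailored feedback about how their behavior compares to the health norms". Step 6 lets intervention participants do session 1 on a tablet in the practice or at home. Those who do not use the tablet first give only a short questionnaire and an email address, and are then reminded to do session 1. The control arm fills in its baseline questionnaire in the practice or at home.

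**Analysis (Step 6).** The outcomes are changes from baseline in physical activity, fruit and vegetable intake and self-regulation skills, compared by repeated measures MANOVA. Socioeconomic status, age, sex, health status and reaching health norms are compared at baseline, and those that differ become covariates.

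**The concern.** Groups 1 and 2 form the only randomised contrast; Group 3 is recruited by GPs. Two features put that contrast at risk.

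First, the text does not settle how the two arms come about. Randomly selecting people for a control group is not the same as randomly allocating recruited people between two arms. Selecting and motivating people for the other arm is different again.

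Second, even if recruitment and randomisation come first, a full baseline seems to require different things in the two arms: starting a behavior-change program in Group 1, filling in a form in Group 2. An analysis of change from baseline can use only people with a baseline. Group 1 would then be weighted toward people willing to start, and willingness may itself predict later change. The program's own theory (Introduction and Step 2) treats intention as a precursor of behavior change. A difference between arms could then partly reflect who was measured and not what the program did.

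**Working it through.** **1. The plan's own figure.** 15 practices x 30 adults = 450, as stated. Each group has 15 x 10 = 150. The article gives no effect size, SD, intraclass correlation, power or dropout, so no power calculation can be reproduced. For scale only: 150 v 150, two-sided 0.05, 80% power, no clustering or dropout, detects (1.960 + 0.842) x sqrt(2/150) = 0.32 SD.

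**2. The accounts of group formation, side by side.**

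| Place in Step 6 | Group 1 | Group 2 |
|---|---|---|
| Opening description | recruited, then randomised | recruited, then randomised |
| Arm descriptions | selected and motivated to use the program | randomly selected; questionnaire only |
| Numbers per practice | 10 selected and allocated | 10 selected and allocated |

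The first and third rows are compatible with selecting 20 people and splitting them at random. The second row is not, if read as a description of recruitment. That reading has some support: Step 6 uses nearly the same phrase for how GPs select and motivate Group 3, and there it plainly describes recruitment.

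**3. What a baseline record requires.** In Group 1 the behavior questionnaire opens session 1, so someone who never starts session 1 appears to leave at most the short questionnaire, whose content is not described. In Group 2 the questionnaire stands alone. The Introduction says that few people start Internet-delivered interventions, which gives a reason to expect unequal completion.

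**4. Illustration of size.** Every input here is an assumption; none is in the article. Let r1 and r2 be the shares of Groups 1 and 2 that yield a full baseline. Let rho be the correlation between willingness to start and the outcome change. Assume those who start are the most willing, on a normal scale. Then

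bias in SD units = rho x [phi(c1)/r1 - phi(c2)/r2],

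where phi is the standard normal density and c the cut-off that leaves a share r above it. The term phi(c)/r is 0.195 at r = 0.9, 0.350 at 0.8, 0.644 at 0.6 and 0.966 at 0.4. The type I error is for a two-sided z test at 0.05, with 150 x r1 and 150 x r2 people and no clustering.

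| r1 | r2 | rho | Bias (SD) | Type I error |
|---|---|---|---|---|
| 0.9 | 0.9 | any | 0 | 5.0% |
| any | any | 0 | 0 | 5.0% |
| 0.8 | 0.9 | 0.2 | 0.03 | 5.7% |
| 0.6 | 0.9 | 0.2 | 0.09 | 10.1% |
| 0.4 | 0.9 | 0.2 | 0.15 | 16.9% |
| 0.8 | 0.9 | 0.3 | 0.05 | 6.6% |
| 0.4 | 0.9 | 0.3 | 0.23 | 32.0% |

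Example: 0.2 x (0.644 - 0.195) = 0.09 SD. If uptake were the other way round (r1 = 0.9, r2 = 0.8, rho = 0.2), the bias would be -0.03 SD.

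**5. Whether the planned adjustment helps.** None of the five listed characteristics measures motivation or intention, and each enters only if it differs at baseline. Adjustment for them cannot be relied on to remove selection on willingness to change.

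**The case against.** The strongest reply is that the explicit sequence is recruit, then randomise, and that the sentence on numbers per practice uses the same wording for both arms. On that reading the flyer or tablet is simply how the intervention reaches people already allocated to Group 1. Group 2 is a waiting list, so its members may have been recruited with the program in prospect. The article also says in Methods that it is not the trial's research protocol and describes the evaluation only briefly, and the design diagram (Figure 4) is not shown. Consent order, invitation text and concealment may be set out elsewhere, and their absence here is not a fault.

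Much of this stands. A reader might infer that the arms are told apart at the invitation, by one researcher who knows the arm, in a single waiting-room contact, with refusers replaced until 10 and 10 are reached, and so that Groups 1 and 2 are not comparable. The article does not support that. It mentions the waiting room only for Group 3, does not say that the recruiter knows the arm in advance, and gives no replacement rule. Nor does any one sentence state that baseline follows allocation; that is inferred from Steps 4 and 6 together.

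Two things survive. The arm descriptions conflict with the opening sentence whatever the full protocol says. And the benign reading does not deal with the baseline: even with proper randomisation, a full Group 1 record still appears to depend on starting session 1.

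**Conclusion.** The concern holds as an inconsistency and a risk, not as a demonstrated bias. Step 6 describes the formation of the only randomised contrast in ways that cannot all be followed. Steps 4 and 6 together indicate that baseline comes after allocation and is conditional on program start in one arm only.

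The size is unknown. It is zero if completion is equal in the two arms or if willingness is unrelated to change, and slightly negative if Group 2 completes less often. It reaches about 0.2 SD under the most unequal uptake assumed (40% v 90%, rho = 0.3). It could therefore be negligible, or a substantial part of the 0.32 SD that 150 per arm could detect at best. These figures rest wholly on assumed uptake and correlation. The correction is cheap and belongs before recruitment, because baselines not collected then cannot be recovered later.

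**What to change.** State one sequence in Step 6 and use it throughout:

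1. The researcher recruits 20 patients per practice with the same invitation.
2. All 20 complete the same baseline behavior questionnaire, on the tablet or at home.
3. Only then does random allocation, not visible to the recruiter beforehand, open either session 1 feedback and encouragement (Group 1) or the waiting list (Group 2).
4. Everyone randomised is analysed in the allocated group.

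In the arm descriptions, replace the wording about selecting (Group 1) and random selection (Group 2) with random allocation.

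Costs: Group 2 also needs personal codes, which Step 6 mentions only for the intervention groups, and the LimeSurvey program needs a branch after the questionnaire. Some patients will complete a baseline before learning their arm. Group 1's recruitment also becomes less like that of the GP-recruited, non-randomised Group 3, which weakens the planned comparison of GP with researcher involvement unless Group 3 also completes the baseline questionnaire before starting the program.

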In Step 6—evaluation—it will be investigated whether the direct involvement of GPs in the program matters. More specifically, we will evaluate whether GPs’ involvement leads to more sustained use of the intervention and higher levels of PA and FV intake. Also, multilevel analyses will be conducted to control for the clustering of participants into different general practices. Furthermore, it will also be important to evaluate the quality of participants’ action plans because previous research has shown that action plans of participants can be of poor quality [58].

Following the IM protocol is a complex and time-consuming enterprise [44,59]. Therefore, we suggest that future researchers search for existing study protocols that describe the development of interventions and integrate similar theories and methods that can be used as the basis for their intervention programs. In our study, existing protocols were used to translate self-regulation methods into practical applications in a computer-tailored program [25,26,41]. However, as target behaviors and contexts differ, it is important to further elaborate the different steps of the IM protocol for new interventions. Our program, for example, differs from the existing protocols in several ways. First, we used a program that made it possible to deliver tailored follow-up feedback in which changes in health behavior were mentioned and compared with health goals. This makes it possible to provide detailed tailored feedback on the behavior change process. Second, the delivery mode of our program is variable, as the program can be delivered via different channels, such as via the Internet and via tablets. The delivery via tablets made it possible to deliver MyPlan 1.0 in natural settings (ie, general practice). This leads us to the third important aspect on which our program deviates from other programs [25,26,41], namely, the possibility to integrate extra personal feedback by general practitioners. In conclusion, if MyPlan 1.0 is found to be effective, a new eHealth program for the promotion of PA and FV intake that can be applied by GPs will be available. Future research can focus on designing modules for other behaviors and on evaluating other methods and effective channels for implementation.

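### Group 3 is recruited by GPs, afterwards and without random allocation, so it cannot show what GP involvement causes; the effectiveness test should be stated as Group 1 v Group 2 only

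*Protocol article*

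**What the plan says.** All of this stands in the Protocol article; no other document is at hand.

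- **Design label** (Step 6: Evaluation of the Program): "A clustered quasi-experimental trial with three conditions will be used to evaluate the intervention".
- **Groups 1 and 2** (Step 6): a researcher recruits the patients and allocates them at random between intervention and waiting-list control, 10 and 10 per practice.
- **Group 3** (Step 6): GPs recruit straight into the intervention once the researcher has finished: "Next, GPs will be asked to recruit another 10 patients to complete the intervention program". On how patients are found, the text says: "In Group 3, the selection and motivation of adults will be randomly conducted by GPs in the waiting room". The Figure 4 legend confirms that the recruiter differs by group.
- **Inference** (Step 6, repeated in the Discussion): the evaluation is to show whether GPs' "involvement leads to more sustained use of the intervention and higher levels of PA and FV intake".
- **Analysis** (Step 6): changes from baseline are compared between control and intervention conditions by repeated measures MANOVA. Baseline characteristics that differ between intervention and control become covariates. Multilevel analyses handle practice. No sentence says whether Groups 1 and 3 enter separately or together.

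**The concern.** No patient had a chance of landing in either Group 1 or Group 3. Recruiter, the patients that the recruiter approaches, who accepts, and order of recruitment all change together with GP involvement. A GP may approach patients who are more motivated, or who have more to gain, than those whom a researcher would approach. A difference between Groups 3 and 1 would then appear with no effect of involvement at all, and the plan would read it as an effect.

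Sustained use is the most exposed outcome. The control group has no access to the programme during the comparison, so use can be compared only between Groups 1 and 3. Use also has no baseline value, so analysing change from baseline gives it no protection.

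The second risk is to the main result. Two of the three groups are intervention groups, but the outcome comparison and the covariate rule are both worded as a two-way contrast. An analyst could follow that wording and test Groups 1 and 3 together against Group 2, which would carry any Group 3 selection bias into a comparison that is otherwise randomised.

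**Working it through.** **Inputs from Step 6.** 15 practices, 30 adults each, 10 per group per practice.

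**The plan's own figure.** 15 x 30 = 450, as stated. Per group: 15 x 10 = 150. The article gives no alpha, power, effect size or SD, so there is no power calculation to reproduce.

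**Where the bias goes.** Work in SD units. Let e be the programme effect, g the true effect of GP involvement, and b the difference between Group 3 and researcher-recruited patients that arises from selection and order of recruitment alone.

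- Group 1 − Group 2 = e. Randomised, so b does not enter.
- Group 3 − Group 1 = g + b. The two cannot be separated.
- Pooled Groups 1 and 3 − Group 2 = e + (150/300)(g + b) = e + g/2 + b/2.

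**Illustration of size.** Assumptions: e = g = 0, SD 1, two-sided alpha 0.05, normal approximation, clustering ignored, everyone analysed. The values of b are assumed and show a range only.

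- SE for Group 1 v 2 and for Group 3 v 1: √(2/150) = 0.115.
- SE for pooled v Group 2: √(1/300 + 1/150) = 0.100.
- False-positive rate = P(|Z + shift/SE| > 1.96).

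| Assumed b (SD) | Group 3 v 1 | Pooled shift b/2 | Pooled v Group 2 | Group 1 v 2 |
|---|---|---|---|---|
| 0.1 | 13.9% | 0.05 | 7.9% | 5.0% |
| 0.2 | 41.0% | 0.10 | 17.0% | 5.0% |
| 0.3 | 73.8% | 0.15 | 32.3% | 5.0% |

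If only half of the participants were analysed (also assumed), the rates would be 9.4%, 23.2% and 45.1% for Group 3 v 1, and 6.4%, 10.9% and 18.6% for the pooled test. Group 1 v 2 stays at 5.0%. The rates fall only because the test is less precise; the bias itself is unchanged.

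**The case against.** **The design is disclosed.** The article calls itself quasi-experimental, claims random allocation only between Groups 1 and 2, and names each group's recruiter. That is fair, and nothing presents Group 3 as randomly allocated to an arm. But the label does not support the causal verb used for Group 3, and neither Step 6 nor the Discussion qualifies it.

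**GP selection is called random.** The sentence concerns how patients are approached and motivated in the waiting room, not how they are assigned between arms. Even a truly random draw by the GP would leave Group 3 separately recruited and later.

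**Safeguards exist.** PA and FV intake are analysed as change from baseline, five baseline characteristics are compared, all groups come from the same practices, and multilevel models are planned. This removes practice as an explanation and deals with part of the measured imbalance. However, the covariate rule looks for differences between intervention and control, not between Groups 3 and 1, and motivation is not on the list.

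**The article is not the trial protocol.** It says so in its Methods and describes Step 6 only briefly, so a fuller document may fix the contrasts. That could settle the pooling question. It would not make Group 3 randomised, nor change the inference stated here.

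**Stronger readings that the text does not support.**

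- A reader might infer that pooling is planned. It is not stated, and three conditions plus a question on GP involvement point towards keeping the groups apart. The wording only leaves pooling open.
- A reader might take Step 5, where "GPs can autonomously decide which method is suitable for their own working system, for different patients, and for different circumstances", as licence for selective enrolment. That sentence is about how the programme is delivered, not whom GPs recruit into the trial.
- A reader might infer a seasonal difference from the order of recruitment. The article gives the order but no dates or interval; within a practice the gap could be short.

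**Conclusion.** The point holds in two parts. First, Group 3 v Group 1 is a non-randomised comparison of separately and successively recruited patients, so the stated conclusion about what GP involvement leads to cannot be drawn from it. This follows from the recruitment text alone and needs no assumption. Second, the analysis wording does not exclude Group 3 from the effectiveness comparison. This is an ambiguity to close, not a planned error.

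The size depends on b, which the document does not give and whose direction is unknown. What is fixed is the algebra: all of b falls on Group 3 v Group 1, b/2 falls on a pooled estimate (150 of 300 intervention patients non-randomised), and none falls on Group 1 v Group 2. The false-positive rates are illustrations under assumed b, alpha 0.05 and no clustering. The randomised comparison is sound on this point as long as Group 3 stays out of it.

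**What to change.** 1. State in Step 6 that the effectiveness test is the randomised Group 1 v Group 2 comparison (150 v 150) and that Group 3 is not pooled into it.
2. State that Group 3 v Group 1 is a non-randomised comparison. Adjust it for SES, age, sex, health status, reaching health norms and baseline behaviour, all of which are already collected, whether or not they differ between intervention and control. Keep the multilevel term for practice.
3. In Step 6 and the Discussion, replace 'leads to' with 'is associated with' for GP involvement.

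Recruitment, patient numbers and data collection do not change. The cost is a weaker stated conclusion on GP involvement, and the adjustment covers only measured differences.
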